CQI field activities for the entire project were scheduled in advance of the first intervention step. Clinic-based CQI activities occurred over 3 days of a given week, and administrative work scheduled for a separate day each week. CQI tools and principles (Tables 1 & 2) included Action Learning Sessions at the end of each transition phase to consolidate skills and share experiences. The intervention was based on the Institute for Healthcare Improvement (IHI) breakthrough collaborative CQI model [38]. Given time constraints imposed by the study design, activities mainly targeted the primary endpoint indicators: repeat HIV screening and HIV viral load (VL) testing according to South African PMTCT guidelines (Additional file 1: Text S1). Additional study endpoint indicators were addressed as time permitted.

**Table 2 Tab2:** Description of CQI tools used in the intervention

CQI tool	Description
Process map	A map of clinic processes relating to a specific activity from the time a patient walks into the clinic A map, including waiting times and waiting site, is created for each activity as there may be differences in the process based on clinical need (e.g. a patient who is HIV-positive with tuberculosis co-infection versus a patient who is HIV-positive without tuberculosis). Mapping identifies areas for improved process efficiency, thereby reducing clinical workload and patient waiting times.
Run chart	A display of real-time data on target indicators The run chart is the essence of the ‘data-driven’ approach of CQI. Target indicators, or process indicators, are selected during the early stages of CQI implementation, for monitoring throughout the period of CQI activities. Facility staff can observe the results of changed activities using their own data in real-time on the so-called run chart. The run chart facilitates motivation and buy-in.
Fishbone diagram	A diagrammatic representation of factors contributing to a specific clinical endpoint – a ‘cause and effect’ diagram
PDSA cycle [44]	A representation of the process of change In the Planning stage, facility staff (guided by CRH CQI mentors) plan how to implement change targeting a specific endpoint (Plan). This is followed by actual implementation (Do) and review of progress and challenges (Study). The change becomes embedded in normal practice if implementation was successful, or generates a different method of implementation (Act).

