#### Data sources

All eligible women had their Maternity Case Record (MCR) photographed at delivery, excluding the intrapartum section, based on UKZN Biomedical Research Ethics Committee waiver of requirement for consent to access routine DoH data. All consenting women were interviewed at delivery and their infant’s Road-to-Health Booklet (RtHB) photographed. The structured interview covered themes on demographics, satisfaction with services, obstetric history, pregnancy intention, healthcare expenditures, access to care, and knowledge (infant feeding and HIV). At the 3–6 day and 6-week postnatal visits all consenting women were interviewed and their infant’s RtHB photographed. The structured interview at the 3–6 day visit was identical to the delivery visit. The 6-week structured interview covered themes on demographics, satisfaction with services, knowledge and uptake of services (HIV, PMTCT services, adherence to ART, contraception, self-reported infant feeding practices), healthcare expenditures, and access to care. All questionnaires contained questions in English with isiZulu translations and were conducted in isiZulu.

Structured interviews of consenting healthcare providers at the 7 study clinics were undertaken in English covering themes on job satisfaction, motivation and antenatal care practices, at study mid-point and study end.

Process evaluation data sources included semi-structured healthcare provider interviews undertaken in English, and detailed CQI implementation records from CRH for each PHC. The latter included actual visit dates, visit type, and descriptions of the successes and challenges the CRH CQI mentors encountered in implementing CQI.

Data collection from clusters commenced on 15 July 2015 and concluded on 30 January 2017. Each cluster contributed pre-exposure data until rolled over to the CQI intervention. Data collection continued from all clusters throughout the study until project end, providing pre-exposure, transition phase and post-exposure outcome data on all clusters.

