As women were recruited at delivery or thereafter starting on 15 July 2015 - with retrospective capturing of their routine antenatal care data – the 2-month baseline data collection period contributed an additional observation period of ~ 6 months, resulting in a total data collection period of ~ 19 months and total observation period of ~ 25 months. The final post-exposure period (after all clusters had received the intervention) was 4.5 months (Fig. 2).

Eleven data clerks trained in International Conference on Harmonisation (ICH) Good Clinical Practice (GCP) guidelines were based at either Hlabisa Hospital or the 7 PHCs throughout the study. All data collected in clinics and Hlabisa Hospital, including cameras, were returned daily to the AHRI data centre for secure storage and capturing. A data capturing team of five trained in ICH GCP, including research nurses and quality controllers, captured clinical and laboratory data from digital photographs of MCRs and infant RtHB, and all information from structured questionnaires onto a REDCap™ study database [39].

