### Analysis

#### Power calculation

For our baseline power calculation, we assumed – based on local routine primary care data – that without the MONARCH intervention viral load testing would be carried out in 40% of all pregnant women who were HIV-positive and repeat HIV testing would be carried out in 65% of all pregnant women who were HIV-negative. Based on local routine primary care data, we further assumed that half of all pregnant women would be HIV-positive and that pregnant women would make three ANC visits. We assumed an intracluster correlation coefficient (ICC) of 0.10. This coefficient is conservative compared to ICCs that we empirically measured in a similar setting (PHCs in sub-Saharan Africa providing ANC and HIV treatment and care), which ranged from 0.00 to 0.07 [40]. Finally, we assumed that we could not use information from 15% of enrolled women because of missing data. Given these assumptions, we estimated that we would have 80% power to detect at least a 15 percentage point increase in our two primary endpoints at the 5% significance level if we enrolled a total of 1260 pregnant women (i.e., 630 women who were HIV-positive and 630 women who were HIV-negative). Additional file 1: Table S1 shows the minimum detectable differences for this sample size with a number of alternative ICCs and endpoint values in the control exposure state.

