#### Statistical analysis

The data will be analyzed by intention-to-treat (ITT). For ITT analyses, patient outcomes will be analyzed by the exposure status of the clinic attended at the first antenatal booking visit, independent of later clinic switches. We will analyse the CQI effect using mixed effects generalized linear regression models. In the main analysis, we will include a fixed effect for the time step and a random effect for clinic, following Hussey and Hughes [41], as well as adjust for clustering of standard errors at the clinic level. For the analyses of our two primary endpoints, which are binary, we will use modified Poisson regression [42] within the generalized linear regression framework. Our main results will thus be expressed as risk ratios. In sensitivity analyses, we will adjust for patient pre-exposure characteristics, and we will assess effect modification by secular time and time since intervention start in a clinic [43]. Stata (version 15.0, StataCorp, College Station, Texas) will be used for all analyses.

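### Virologic suppression and HIV seroconversion are seen only through the routine tests that CQI aims to increase, so a CQI effect on them cannot be separated from a CQI effect on testing

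*Protocol article*

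**What the plan says.** The section on primary and secondary endpoints lists, among maternal health outcomes, virologic suppression in women who are HIV-positive and seroconversion in pregnancy in women who are HIV-negative. It names these populations but does not say how a woman without a test result is counted.

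Under Data sources, the maternity case record is photographed at delivery under a "waiver of requirement for consent to access routine DoH data", and staff "captured clinical and laboratory data from digital photographs of MCRs and infant RtHB". The article describes this as "retrospective capturing of their routine antenatal care data". It describes no study blood sample, no study HIV test, and no linkage to laboratory or surveillance data for these outcomes.

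Under Intervention package, "activities mainly targeted the primary endpoint indicators: repeat HIV screening and HIV viral load (VL) testing". Under Power calculation, the control-state assumptions are that "viral load testing would be carried out in 40% of all pregnant women who were HIV-positive" and that "repeat HIV testing would be carried out in 65% of all pregnant women who were HIV-negative", with "80% power to detect at least a 15 percentage point increase in our two primary endpoints at the 5% significance level".

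Under Statistical analysis, the general statement is "We will analyse the CQI effect using mixed effects generalized linear regression models"; modified Poisson regression is then named for the two primary endpoints. The limitations in the Discussion cover service pressure, advance publicity and contamination. They do not mention that these two outcomes are observed through the intervention's own target.

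**The concern.** Each primary endpoint is the means of observing a secondary one. A suppressed viral load is recorded only if a viral load was measured, and a seroconversion only if a repeat HIV test was done. At the planning rates, 60% of HIV-positive women and 35% of HIV-negative women would have no result in the control state. If CQI works, fewer would lack one in the intervention state (45% and 20%).

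A difference between exposure states in either outcome therefore mixes two things: a change in who is tested, and a change in suppression or infection. Both are listed as maternal health outcomes, so a difference is open to being read as the second when it may be wholly or partly the first. Two of the three listed limitations are described as biasing towards the null. If untested women are coded as having no event, this one biases away from it.

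**Working it through.** **Inputs from the documents.** Viral load testing 40%, repeat HIV testing 65%, rise of 15 points in each, 630 women per endpoint, 15% unusable, ICC 0.10 (Power calculation); six clusters crossing over one at a time after a baseline period (Randomisation and blinding); 20–40% virologic failure among women on ART, and HIV incidence in pregnancy and postpartum above 4% (Background).

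**Assumptions.** True suppression 60–80%, which applies the figure for women on ART to all HIV-positive women. True seroconversion 4%, with a range of 2–6%. No true change in either outcome. Two-sided 5% test.

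**The plan's own power figure.** The Hussey–Hughes formula with 630 × 0.85 = 535.5 analysable women gives about 53–59% power for 40% to 55% and 56–67% for 65% to 80%, depending on how the variance and ICC are parameterised. The stated 80% was not reproduced. The role of the assumed three visits is not explained, so the article's method cannot be recovered. That is a separate matter, and nothing below depends on it.

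**A. Untested women counted as having no event.** Recorded proportion = P(tested) × P(event).

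| Outcome | True rate | Control | CQI | Risk ratio |
|---|---|---|---|---|
| Suppression | 60% | 0.40 × 0.60 = 24.0% | 0.55 × 0.60 = 33.0% | 1.375 |
| Suppression | 70% | 0.40 × 0.70 = 28.0% | 0.55 × 0.70 = 38.5% | 1.375 |
| Suppression | 80% | 0.40 × 0.80 = 32.0% | 0.55 × 0.80 = 44.0% | 1.375 |
| Seroconversion | 4% | 0.65 × 0.04 = 2.6% | 0.80 × 0.04 = 3.2% | 1.23 |

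The true rate cancels: the risk ratios are 0.55/0.40 = 1.375 and 0.80/0.65 = 1.23 whatever it is.

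**B. Chance that the artefact is significant.** Take I = 6 equal clusters and T = 7 equal periods, a linear model, and 535.5/42 = 12.75 women per cluster-period. The design sums are U = 21, W = 91, V = 91.

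Var = Iσ²(σ² + Tτ²) / [(IU − W)σ² + (U² + ITU − TW − IV)τ²]

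The two brackets' coefficients are 126 − 91 = 35 and 441 + 882 − 637 − 546 = 140.

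At 70% true suppression:
- Mean binomial variance = (0.28 × 0.72 + 0.385 × 0.615)/2 = 0.2192.
- τ² = 0.10 × 0.2192 = 0.0219; σ² = 0.90 × 0.2192/12.75 = 0.01547.
- SE = 0.0659; z = 0.105/0.0659 = 1.59; rejection probability 0.357.

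At 60% and 80% true suppression it is 0.296 and 0.425. The other common ICC parameterisation (full binomial variance within clusters) gives 0.27–0.39. Overall this is about 27–42%, against a nominal 5%.

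For seroconversion at 4%, SE = 0.0236, z = 0.006/0.0236 = 0.25, and the two-tailed rejection probability is about 6% (5–6% for incidence of 2–6%). About 14–17 detected events would be expected (2.6–3.2% of 535.5).

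**C. Tested women only.** The result depends on the extra 15 points of women who are tested.
- Suppression, 70% among those already tested: if the newly tested are 50% suppressed, (0.40 × 0.70 + 0.15 × 0.50)/0.55 = 64.5%, risk ratio 0.92. If 90%, (0.28 + 0.135)/0.55 = 75.5%, risk ratio 1.08. If 70%, 1.00.
- Seroconversion, 4% among those already retested: if the newly tested have half the risk, (0.65 × 4% + 0.15 × 2%)/0.80 = 3.63%, risk ratio 0.91. If double, (2.6% + 1.2%)/0.80 = 4.75%, risk ratio 1.19.

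**The case against.** *The denominator belongs to the analysis plan.* The article names populations and does not say that untested women count as events or non-events. Handling of missing secondary outcomes is commonly specified elsewhere, so its absence is not the point. What stands is structural: no choice of denominator recovers the results of untested women. One choice makes the outcome scale with testing, and the other conditions on something that CQI changes.

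*A reader might infer that the trial would report better suppression and more HIV infection, the latter looking like harm.* The documents do not support this. Those directions need untested women to be coded as having no event, which the article does not state. Among tested women the sign is unknown and the bias can be zero. The seroconversion artefact would be significant about 6% of the time, hardly above the nominal level.

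*Some of a rise in suppression could be genuine.* The Background gives a route from viral load testing to suppression, through adherence counselling, resistance testing and treatment switches. This is correct. The defect is that the two effects cannot be told apart, not that any rise must be an artefact.

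*The rejection probabilities are simplified.* They assume equal clusters although clusters were stratified by volume, equal periods although the endline lasts 4.5 months, and a linear model. They are indicative. The risk ratios under A need none of these assumptions.

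*Other data may exist.* The setting has population HIV surveillance, and women are interviewed. No surveillance linkage is described for these endpoints. The listed interview themes would not yield a viral load, and a self-reported new diagnosis would itself depend on testing.

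**Conclusion.** The point holds for these two secondary endpoints. As the article describes ascertainment, a CQI effect on suppression or seroconversion is not identifiable separately from a CQI effect on testing.

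Counting untested women as having no event yields spurious risk ratios of 1.375 and 1.23 from the planned rise in testing alone. For suppression this carries a material chance of a false significant result, about 27–42% under the simplified model and the assumed 60–80% suppression. For seroconversion the consequence is mainly a biased estimate. Restricting to tested women replaces this with a selection bias of unknown direction, which is absent only if newly tested women resemble those already tested.

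This does not affect the validity of the primary endpoints, for which testing is itself the outcome. It should be dealt with before the secondary results are interpreted, but it does not undermine the trial.

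**What to change.** 1. Relabel the outcomes as 'tested and suppressed', a care-cascade measure, and 'new HIV infections detected on repeat testing'.
2. By exposure state, show all HIV-positive women as tested and suppressed, tested and not suppressed, or not tested. Do the same for HIV-negative women (retested and newly positive, retested and negative, not retested), with testing coverage alongside.
3. Give best- and worst-case bounds for untested women. They will be wide. With 70% suppression among tested women, true suppression could lie between 28% and 88% at 40% coverage (28% + 60%), and between 38.5% and 83.5% at 55% coverage (38.5% + 45%). That width is an honest statement of what the data can show. Weighting tested women by the inverse of their probability of being tested is an optional sensitivity analysis, if the record holds adequate predictors.
4. State that a change in either measure will not be interpreted as a CQI effect on true suppression or incidence.

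A rate per woman retested should not be the main measure, because it conditions on testing. Nor should any rise be declared in advance to be extra detection: among retested women, higher coverage alone does not raise the proportion.

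The cost is analysis-plan wording and some tabulation of data already captured. The downside is less favourable and less definite statements on these two outcomes.

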#### Randomisation and blinding

Each clinic was a cluster, with the exception of the two smallest clinics, which jointly formed one cluster. After a baseline data collection period of 2 months, the first cluster crossed over from control to intervention exposure state on 29 September 2015; subsequently, one additional cluster crossed over every 2 months (Fig. 2). The six clusters were divided into 3 groups by patient volume (low, medium and high). To increase the likelihood that the sample sizes in intervention and control exposure states were similar, and to improve balance, we then randomised the clusters to the six calendar sequences of crossing over, such that both the first three and the last three sequences included one small, one medium, and one large cluster. A senior biostatistician performed randomisation for all clusters prior to the first intervention step. All study implementers, evaluators and clinic health workers were blinded to the initial randomisation status. Two weeks prior to each scheduled intervention step crossover date, the custodian of the randomisation list (AHRI Chief Information Officer) revealed the randomised cluster to the AHRI study team. The AHRI study team then introduced the CRH team to the randomised cluster for CQI training to commence.

### Analysis

#### Power calculation

For our baseline power calculation, we assumed – based on local routine primary care data – that without the MONARCH intervention viral load testing would be carried out in 40% of all pregnant women who were HIV-positive and repeat HIV testing would be carried out in 65% of all pregnant women who were HIV-negative. Based on local routine primary care data, we further assumed that half of all pregnant women would be HIV-positive and that pregnant women would make three ANC visits. We assumed an intracluster correlation coefficient (ICC) of 0.10. This coefficient is conservative compared to ICCs that we empirically measured in a similar setting (PHCs in sub-Saharan Africa providing ANC and HIV treatment and care), which ranged from 0.00 to 0.07 [40]. Finally, we assumed that we could not use information from 15% of enrolled women because of missing data. Given these assumptions, we estimated that we would have 80% power to detect at least a 15 percentage point increase in our two primary endpoints at the 5% significance level if we enrolled a total of 1260 pregnant women (i.e., 630 women who were HIV-positive and 630 women who were HIV-negative). Additional file 1: Table S1 shows the minimum detectable differences for this sample size with a number of alternative ICCs and endpoint values in the control exposure state.

#### Statistical analysis

The data will be analyzed by intention-to-treat (ITT). For ITT analyses, patient outcomes will be analyzed by the exposure status of the clinic attended at the first antenatal booking visit, independent of later clinic switches. We will analyse the CQI effect using mixed effects generalized linear regression models. In the main analysis, we will include a fixed effect for the time step and a random effect for clinic, following Hussey and Hughes [41], as well as adjust for clustering of standard errors at the clinic level. For the analyses of our two primary endpoints, which are binary, we will use modified Poisson regression [42] within the generalized linear regression framework. Our main results will thus be expressed as risk ratios. In sensitivity analyses, we will adjust for patient pre-exposure characteristics, and we will assess effect modification by secular time and time since intervention start in a clinic [43]. Stata (version 15.0, StataCorp, College Station, Texas) will be used for all analyses.

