**Methods:**

This is a stepped-wedge cluster-randomised controlled trial (RCT) of 7 nurse-led primary healthcare clinics to establish the effect of CQI on selected routine antenatal and postnatal services. Each clinic was a cluster, with the exception of the two smallest clinics, which jointly formed one cluster. The intervention was applied at the cluster level, where staff received training on CQI methodology and additional mentoring as required. In the control exposure state, the clusters received the South African Department of Health standard of care. After a baseline data collection period of 2 months, the first cluster crossed over from control to intervention exposure state; subsequently, one additional cluster crossed over every 2 months. The six clusters were divided into 3 groups by patient volume (low, medium and high). We randomised the six clusters to the sequences of crossing over, such that both the first three and the last three sequences included one cluster with low, one with medium, and one with high patient volume.

The primary outcome measures were (i) viral load testing among pregnant women who were HIV-positive, and (ii) repeat HIV testing among pregnant women who were HIV-negative. Consenting women ≥18 years attending antenatal and postnatal care during the data collection period completed outcome measures at delivery, and postpartum at three to 6 days, and 6 weeks. Data collection started on 15 July 2015. The total study duration, including pre- and post-exposure phases, was 19 months. Data will be analyzed by intention-to-treat based on first booked clinic of study participants.

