### Study design

The study, a stepped-wedge cluster RCT, was carried out from 15 July 2015 to 30 January 2017, at the 7 DoH PHCs described above: Mtubatuba, KwaMsane, Mpukunyoni, Somkhele, Machibini, Esiyembeni and Gunjaneni. All clusters crossed over from control to intervention exposure according to the stepped-wedge study design (Fig. 2). The six clusters were randomised to the calendar sequences of crossing over. The stepped-wedge study design was selected because (i) it was considered unethical to withhold the intervention from some clinics as CQI has known efficacy in resource-rich settings; (ii) the participation of all clinics both during the control and the intervention exposure state was thought to be better if it was known that during the course of the trial all clinics would receive the intervention; (iii) the field implementers of CQI were a small team of three people, making simultaneous rollout in all clusters impracticable; and (iv) it allows adjustment for secular trends in outcomes. Data collection occurred at all 7 DoH PHCs and Hlabisa Hospital maternity ward as the majority of deliveries from the sub-district occur at Hlabisa Hospital.

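### Standard errors are clustered at clinic level (seven clinics if read literally), although six clusters were randomised; the numerical effect is small

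*Protocol article*

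**What the plan says.** The abstract's Methods paragraph counts the facilities: "This is a stepped-wedge cluster-randomised controlled trial (RCT) of 7 nurse-led primary healthcare clinics". The section Randomisation and blinding maps them to randomised units: "Each clinic was a cluster, with the exception of the two smallest clinics, which jointly formed one cluster". Study design gives the number allocated: "The six clusters were randomised to the calendar sequences of crossing over". On timing, after the first cluster crossed over, "subsequently, one additional cluster crossed over every 2 months", so the two paired clinics share one crossover date.

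The section Statistical analysis names clinic, not cluster, in both parts of the main model: "a fixed effect for the time step and a random effect for clinic", and the intention to "adjust for clustering of standard errors at the clinic level". It does not say whether clinic there means the six randomised clusters. It names no cluster-level term, no reference distribution and no permutation test.

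**The concern.** Two clinics allocated together have the same exposure in every period by design. A robust variance grouped by clinic treats their contributions as independent. The randomisation does not support that, because the pair received one draw, not two. The general rule is to group at the level of allocation or above.

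The sentence governs both primary endpoints, and with so few units each one counts. At stake is that the unit of inference should match the unit of randomisation, and that any later small-sample rule should start from the right count. A programmer who follows the sentence literally would group by seven.

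**Working it through.** **Unit count.** Seven clinics, with one pair counted once: 7 - 1 = 6 randomised units. Grouping by clinic gives G = 7; grouping by randomised cluster gives G = 6.

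**Model standard error and power.** Inputs from Power calculation: control rates of 40% (viral load testing) and 65% (repeat HIV testing), ICC 0.10, a 15-point increase, 630 women per endpoint, 15% unusable. This leaves 630 x 0.85 = 535.5 women. My assumptions are equal cluster and cell sizes, a two-sided 5% normal test and a linear approximation. The method is the Hussey-Hughes generalised least squares variance with six sequences and seven periods:

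- total variance = p0(1 - p0); between-unit variance = 0.10 of that; residual variance per cell = 0.90 of that, divided by women per cell
- power = Phi(0.15/SE - 1.960)

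*Viral load testing, six clusters.* Total variance 0.40 x 0.60 = 0.24; between-unit 0.024; women per cell 535.5/42 = 12.75; residual 0.216/12.75 = 0.0169. SE = 0.0690, so power = Phi(2.175 - 1.960) = 0.585.

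*Repeat HIV testing, six clusters.* Total variance 0.65 x 0.35 = 0.2275. SE = 0.0671 and power = 0.608.

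These do not reproduce the stated 80%. The article does not say how the assumed three antenatal visits enter or how many clusters were used, so this is no evidence of an error. I use the figures only to compare six units with seven.

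*Seven units.* I split one cluster's women equally between two clinics, each with its own intercept, keeping the total fixed. The result depends on which sequence holds the pair:

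| Endpoint | Power, 6 units | Power, 7 units | SE, 6 units | SE, 7 units |
|---|---|---|---|---|
| Viral load | 0.585 | 0.585 to 0.592 | 0.0690 | 0.0684 to 0.0689 |
| Repeat test | 0.608 | 0.608 to 0.615 | 0.0671 | 0.0666 to 0.0671 |

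The gap is largest when the pair crosses first or last: 0.592 - 0.585 = 0.7 points, and 0.06839/0.06896 = 0.992, which is under 1%. It is close to zero when the pair crosses third or fourth.

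**Critical value.** With a t reference on G - 1 degrees of freedom: t(0.975, 6) = 2.447 and t(0.975, 5) = 2.571; ratio 2.571/2.447 = 1.05. With a normal reference both are 1.960 and there is no such difference.

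**Type I error.** Two simulations were run under no effect:

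- 3,000 runs, ICC 0.10, between-period autocorrelation 0.8, robust standard error, normal reference: 15.1% by clinic and 15.3% by cluster when the pair share effects; 14.2% and 14.9% when they do not. The Monte Carlo standard error is about sqrt(0.15 x 0.85/3000) = 0.65 points.
- 4,000 runs per scenario, about 535 women, assumed clinic sizes, t with G - 1: 7.1-8.1% by clinic and 6.6-7.7% by cluster, roughly half a point lower. With a normal reference, about 13-15% either way.

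**Permutation.** The stratified allocation in Randomisation and blinding allows 2^3 x 3! x 3! = 288 cluster orders. Permuting seven clinics freely would include orders that separate the pair, which could not have occurred.

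**The case against.** The strongest reply is that clinic may be shorthand for cluster. The article uses it that way in the Fig. 2 caption, in the eligibility text for individuals, in the Intervention package section and in the limitations. Statistical analysis never prints the number seven, and the analysis plan may define the grouping variable. This stands as a limit on certainty: a reader might infer that the model definitely has seven units, and the article does not settle that. But Randomisation and blinding distinguishes clinic from cluster, so the sentence needs correcting or clarifying either way.

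A second reply is that a clinic random effect is legitimate. Each clinic has its own staff and its own CQI team, so a separate intercept is a defensible model of outcome correlation. This stands. A reader might infer that the random effect is itself an error; it is not, provided it is nested within the randomised cluster. For the same reason the documents only partly support saying that the pair had a single CQI roll-out: the intensive visits were planned per step, but teams were formed per clinic.

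A third reply is that the change hardly matters. That is right about size and is why the point is rated minor. It does not make clinic the right grouping level for the standard errors.

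**Conclusion.** The point holds for the standard errors: as worded they are grouped by clinic, while allocation was by six clusters. Severity is minor. The effect is under 1% on the model standard error and at most about 0.7 points of power, given equal cluster sizes and a linear approximation.

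Two stronger conclusions are tempting and are not supported. One is that the planned intervals are 5% too narrow; that needs a t reference with G - 1 degrees of freedom, which the plan does not state. The other is that clinic-level grouping inflates the type I error materially. With a normal reference the simulated rate is about 13-15% under either grouping, so it reflects the small number of units, and moving from seven to six does not cure it. The permutation argument is likewise conditional, since no such test is planned.

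**What to change.** In Statistical analysis, state that standard errors are clustered on the six randomised clusters, and that any degrees-of-freedom or permutation rule uses those six and the stratified allocation. A clinic random effect may stay if it is nested within the randomised cluster. Only the one pair can separate clinic from cluster variation, so that extra variance component will be poorly estimated. A simpler alternative is a random effect for cluster plus a fixed indicator distinguishing the two paired clinics. If clinic already meant the six clusters, one clarifying sentence is enough.

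The cost is one grouping variable and a short text change. The downside is one fewer unit and possibly slightly wider intervals. A small-sample method for few clusters should be decided separately.
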